**3.0 PRODUCT OVERVIEW**

**3.1 Background and rationale**

Early studies in adult volunteers evaluating live recombinants were based on vaccinia virus that expressed HIV envelope (gp160) antigen. These studies demonstrated that priming vaccinia-naive volunteers twice by scarification with a live vaccinia virus-gp160 recombinant (HIVAC-1e, Oncogen/Bristol Myers Squibb Inc.) elicited CD8+ CTL activity in 45% of the vaccines. Smallpox vaccination with standard vaccinia has been generally regarded as safe, however, serious post-vaccinia complications including fatal vaccinia necrosum (progressive vaccinia) in immunocompromised persons, encephalitis, disseminated vaccinia, and autoinoculation of the eyes have been observed occasionally. Enthusiasm for wide-scale use of a recombinant vaccinia virus vaccine for prevention and control of HIV infection has been tempered by issues of safety and the possibility of transmission of vaccinia virus to close contacts. To circumvent these safety issues, an avian poxvirus vector (canarypox virus) satisfies many of the criteria for an HIV vaccine. Like vaccinia virus, canarypox can accommodate large amounts of foreign DNA in its genome, infect mammalian cells and cause them to produce foreign proteins and is thermostable at ambient temperatures. In contrast to vaccinia virus, canarypox virus is host-range restricted. In mammalian cells, it undergoes an abortive cycle of replication and does not produce infectious progeny virus. Intracellular processing of canarypox-expressed foreign HIV proteins via the MHC Class I pathway leads to induction of cytotoxicT-lymphocyte activity. High doses of canarypox virus have not caused adverse effects in a wide variety of animals, even in profoundly immunosuppressed animals. This means that canarypox recombinants cannot disseminate and cause progressive disease in human recipients or be transmitted to unvaccinated contacts. Canarypox vectors have been safely administered to thousands of volunteers, including HIV-infected persons.

##### 3.2 Human experience with ALVAC vectors

As of Nov-2002, ALVAC candidate vaccines have been administered to over 2000 HIV seronegative individuals expressing proteins from rabies (N=285), measles (N=65), CMV (N=70), Japanese encephalitis (N=12), or HIV (N>1800). Five different ALVAC-HIV vaccine constructs have been studied in over 20 placebo-controlled, double blind trials. These studies have been conducted in the Americas, EU, Africa and Thailand and have involved various HIV risk strata and age groups, including infants. ALVAC has been administered in combination with subunits (rgp160, rgp120), p24, Remune™, DNA vaccines, and to vaccinia primed volunteers*.* In addition ALVAC-HIV vaccines have been used in over 300 HIV-1 infected volunteers without significant safety concerns 8.

The recombinant canarypox virus to be used in this study, ALVAC-HIV (vCP205), expresses the products of multiple HIV-1 genes as follows: the gag gene expressing the gag p55 protein of the HIV-1 LAI strain, the protease portion of the pol gene, expressing the p15 protein of the HIV-1 LAI strain, a part of the env gene expressing gp120 of the HIV-1 MN strain, and the anchoring transmembrane region of gp41 glycoprotein of the HIV-1 LAI strain.

ALVAC-HIV (vCP205), has been administered to over 600 healthy human volunteers including infants. A review of the available human experience to date suggests that ALVAC-HIV vaccines are well tolerated and acceptable to volunteers*.* In a study by Belshe, et al. describing the safety and immunogenicity of ALVAC-HIV (vCP205) among ~420 high and low risk HIV seronegative volunteers, the majority of the solicited local and systemic reactions were mild to moderate in intensity9. Six and 9 volunteers reported severe local and systemic reactions respectively*.* None of the volunteers had both severe systemic and local reactions or were excluded from additional vaccinations*.* Moreover, no increase in local and systemic reactions was seen with repetitive dosing*.* Several studies have evaluated various ALVAC-HIV (vCP205) schedules and doses*.* These studies suggest that multiple administrations of ALVAC-HIV (vCP205) are needed for adequate induction of CTL responses and the number of doses administered is a significant predictor of the CTL response rate 10. The net cumulative CTL response rates attributable to vaccination in these studies ranged from 30 to 60% 9,10,11*.* Importantly, CD8+ T cells derived from recipients of ALVAC-HIV (vCP205) vaccine were capable of lysing autologous CD4+ lymphoblasts infected with primary HIV-1 isolates representing genetically diverse viral clades demonstrating a broad pattern of cytolysis and cross reactivity 12.

Please refer to the Investigator’s Brochure for more detail on the safety and immunogenicity of ALVAC-HIV vaccines.

**4.0 EXPERIMENTAL DESIGN**

**4.1 Safety Evaluation**

Assessment of product safety will include clinical observation and monitoring of hematological, chemical, and immunologic parameters. Safety will be evaluated by monitoring participants for local and systemic adverse experiences during the course of the trial. Subjects will be closely observed for 30 minutes after immunization and then monitored in person by study staff 3 days post each immunization. Subjects will receive a diary card to record their temperature and measure local reaction to the injection. Patients will also be advised to maintain phone contact with study staff in the event of an adverse experience. Any phone contact that suggests a study related problem, an immediate in person evaluation will be scheduled. These efforts will focus on the toxicity parameters listed in Section 5.1. Also see Section 6.1 for power calculation for identifying adverse experiences.

**4.2 Immunogenicity Determinations**

The parameters that will be evaluated to determine vaccine immunogenicity include humoral and cellular immune responses to HIV-1. Assays for cellular immune response will primarily focus on CTL activity (see Protocol section 10). Assays for humoral immunity will include quantitation of both systemic and mucosal specific anti HIV antibodies. The selection of systemic and mucosal assays is the result of 3-4 years of developing expertise in the combined labs of [name] in optimizing sensitive detection assays able to be performed with limited numbers of cells acquired from mucosal biopsies.

**4.3 Detection of Intercurrent HIV-1 Infection**

See Section 10.3.1

**5.0 DATA AND SAFETY MONITORING**

- 1. **Risks**

The risks associated with delivery of the ALVAC-HIV (vCP205) in this trial are described in attached Investigators Brochure. The investigators of this project will continuously monitor data collected from the subjects in this project. Particular emphasis will be put on reviewing any adverse experiences that occur in the subjects. The following will be monitored:

1. Toxic reactions at the site of injection: pain, tenderness, erythema, induration, and other subject reported effects.
2. Systemic reactions: fever, muscle ache, headaches, nausea, fatigue, rashes, any hypersensitivity reactions
3. Immune responses: changes in CD4 and CD8 lymphocytes
4. Hematologic measures: changes in CBC, differential, platelets
5. Hepatic/renal functions: ALT, creatinine
6. Other neurologic, gastrointestinal or dermatologic changes
7. Behavioral changes: increases in sexual and other HIV-1 risk behavior
   1. **Adverse Experience Reporting Requirements**

[name]. initially will review all adverse experience reports followed by the independent monitor. The independent monitor designated for the trial is [name] [name] is Director of the UCLA CARE Clinic for HIV/AIDS patients and has conducted numerous ACTG and other clinical trials at UCLA over the past 10 years. He was selected to monitor this trial because of both his clinical as well as clinical trial experience and because he has no financial or other interest in the outcome of the trial. To assure adequate safety monitoring [name] (or his designated stand-in when he is out of area) and the Aventis Pasteur officer will be notified via e-mail of any Serious Adverse Experiences (SAE) as defined in the CFR 312.32 or grade 3 (see Severity Grading table attached) or higher adverse events and the Adverse Experiences Report (AER - attached) form will be completed and submitted within 48 hours. If the SAE or adverse events are grade 4 or 5, the above protocol will be followed with the addition of having the other agents (FDA and DAIDS project/medical officers informed). [name] will follow-up on each incident with [name] and/or the FDA and DAIDS project/medical officers, as appropriate, to determine the subjects’ continued enrollment in the study. [name] will have ultimate local authority to withdraw subjects from the study on the basis of safety concerns. All grade 1 and 2 events will be reported to all parties above at the end of the study. Because of the small number of subjects, intense schedule of individual monitoring and the paced enrollment of new subjects over the first year (due to the complexity of laboratory assays), [name] will receive only individual data as the need arises, rather than aggregate data. [name] will not be reviewing the immunologic data from this study. In addition, all reports will be forwarded to Aventis Pasteur.

1. **STATISTICAL ANALYSIS**

The results of the cellular immunology assays will be analyzed to determine the differences in immune responses at the baseline visit and each post-immunization visit. Comparisons of groups will be performed using either Fisher exact tests (categorical data) or exact Wilcoxon/Kruskal-Wallis tests (continuous data). Longitudinal analyses may be considered if appropriate, but due to small sample sizes these would be largely exploratory. We expect that the immunizations will stimulate significant cellular immune responses in humans and the levels of immune responses will increase as the number of inoculations with the vaccine increases. The relationship of the responses in the mucosa will also be expressed in relationship to those in the blood, e.g., 2-fold more than in the blood; 60% of the level in the blood, to facilitate comparisons between the immune responses in the groin and deltoid groups.

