**1.1 Primary Objectives**

To evaluate the safety of administering ALVAC-HIV (vCP205) vaccinations to healthy adult individuals using a subcutaneous targeted inguinal lymph node (TILN) or deltoid intramuscular vaccination at 1 x 106.87 TCID50 of ALVAC-HIV (VCP205) (Days 0,7,14 & 21)

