The animal model that best mirrors human HIV-1 disease is simian immunodeficiency virus (SIV) infection of rhesus macaques. Previous work on mucosal immunity to SIV in the rhesus model has guided the development of the current protocol. The current protocol is designed to reproduce in humans knowledge learned from the SIV model, in particular, that delivery of immunogen to the groin area can confer protection against SIV infection in a sexual transmission model, while the same immunogen delivered by other routes fails to protect. Total protection against transmission of SIV across the rectal mucosa was achieved in 4 of 7 macaques and partial protection was achieved in the remaining 3 of 7 when immunogen was delivered by targeted iliac lymph node immunizations. Infection occurred in 13 of 14 unimmunized macaques or those immunized by other routes4.

The targeted lymph node route of immunization involves vaccine injection into the subcutaneous tissue near a lymph node. This efficiently uses the host’s antigen presenting cells to deliver antigen to the lymph node where specific immune responses develop that subsequently may protect the host from infection with the pathogen. The iliac and inguinal lymph nodes are the primary draining lymph nodes of the genitourinary and rectal tracts 5,6. Therefore, this protocol will use groin immunizations (SQ, Inguinal region) as the site for delivery of immunizing antigen to nodes draining the rectal mucosa. As the axillary and supraclavicular lymph nodes are those primarily draining the deltoid area and these nodes do not drain rectal mucosal surfaces, their associated non-mucosal drainage region (IM deltoid) will be used as a comparative immunization site/route. No sampling of nodes is planned in this study.

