- Using a 25g 5/8” needle, administer the injections subcutaneously into the groin area avoiding femoral arteries and nerve pathways. Groin injections will be placed unilaterally, medial to the femoral artery, vein and nerve (approximately halfway between the anterior superior iliac spine and the symphysis pubis) and anterior to the horizontal group of superficial inguinal lymph nodes. Immunization site will be unilateral groin delivery. Immunizations #1 and #3 will be administered to the subjects’ right side and immunizations #2 and #4 will be administered to their left.

-or-

- Using a 21g 1” needle, administer the injections intramuscularly into the deltoid region. Deltoid injections will be placed in the midlateral aspect of the deltoid muscle, 5-8 cm inferior to the scapular acromion process and the lateral edge of the clavicle. Immunization site will be unilateral deltoid delivery. Immunizations #1 and #3 will be administered to the subjects’ right side and immunizations #2 and #4 will be administered to their left.
  - 1. **Route of Immunization**

The vaccine or placebo will be administered subcutaneously (1 ml) unilaterally to inguinal region (alternating sides each sequential immunization), medial to the femoral artery, vein and nerve or IM (1 ml) unilaterally to deltoid region (alternating sides each sequential immunization)

- 1. Vaccine Administration Schedule

| Route/Volume of ALVAC-HIV (vCP205) or placebo | IMMUNIZATIONS | | | |
| --- | --- | --- | --- | --- |
|  | 1 (day 0) | 2 (day 7) | 3 (day 14) | 4(day 21) |
| Subcutaneous  or  Intramuscular  1 ml | ALVAC-HIV (vCP205) | ALVAC-HIV (vCP205) | ALVAC-HIV (vCP205) | ALVAC-HIV (vCP205) |
| placebo | placebo | placebo | placebo |

- 1. **Disposal**

Partially-used and empty vials will be destroyed on site after final vaccine accountability is performed by crushing or incineration according to UCLA Environmental Health and Safety biohazard procedures. All expired or unused vaccine vials will be returned to Aventis Pasteur S.A. Study supplies, including partially used vials, will not be administered to other subjects or used for *in vitro* or animal experiments. All used syringes and needles will be placed into a biohazard “sharps” container and disposed of following the designated UCLA procedures for disposal of potentially infectious materials. Disposal of all materials will be done in accordance with UCLA “Safety Procedures-Standard Operating Procedures”.

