**Day 3 (approximately 3 days post immunization; safety)**

- AE assessment
- Note changes in injection site and surrounding area

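### Draining-node reactions are not a named safety item, and the local examination as worded reaches the draining nodes more readily in the groin arm than in the deltoid arm

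*Protocol*

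**What the plan says.** Section 1.1 makes safety the primary objective, "using a subcutaneous targeted inguinal lymph node (TILN) or deltoid intramuscular vaccination". Section 9 places the groin injection "anterior to the horizontal group of superficial inguinal lymph nodes". Section 2.0 gives the drainage of the comparator site, "As the axillary and supraclavicular lymph nodes are those primarily draining the deltoid area", and adds "No sampling of nodes is planned in this study".

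Section 4.1 ties the safety follow-up to one list: "These efforts will focus on the toxicity parameters listed in Section 5.1". The local item of that list is "Toxic reactions at the site of injection: pain, tenderness, erythema, induration, and other subject reported effects" and the systemic item is "Systemic reactions: fever, muscle ache, headaches, nausea, fatigue, rashes, any hypersensitivity reactions". The other items cover CD4 and CD8 cells, blood counts, ALT and creatinine, neurologic, gastrointestinal or dermatologic changes, and risk behavior. None mentions lymph nodes.

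In the Calendar of Studies the local instruction is "Note changes in injection site and surrounding area", given on Days 3, 7, 10, 17, 21 and 24 and at month 6. The Summary of Studies table also marks an injection-site evaluation on Day 14, but none at month 6. No visit names a node examination. A complete physical examination takes place at Day -42. Day 0 and month 12 have a limited clinical evaluation whose content is not given. The diary card covers temperature and the local reaction.

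**The concern.** What is new in this trial is the site. Section 2.0 says that both routes have been used before, and that the groin was chosen to stimulate the inguinal nodes. A reaction in those nodes is therefore the most site-specific safety finding the trial could produce, yet the body text neither solicits it nor asks anyone to look for it.

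The one instruction that might reach the nodes does not do so equally. The inguinal nodes lie directly behind the groin injection. The deltoid drains to a different region. The same words can lead an examiner to feel the draining nodes in one arm and not in the other. Blinding does not correct this: it hides vaccine from placebo, while the examiner sees which site was injected. At stake is whether a tally of node findings by site reflects the vaccine or how closely each arm was examined.

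**Working it through.** **Inputs.** Six vaccinees per site (Section 6.1). The 24% rate is the one that Section 6.1 says 6 subjects can detect with 80% probability. The protocol gives no rate for node reactions, so 24% and 10% are assumptions. So is the share *s* of true deltoid node reactions that is recorded, shown from 1 to 0. True rates are taken as equal at both sites, and groin reactions as fully recorded.

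**The plan's own figures.** P(at least one event) = 1 - (1 - p)^n.
- p = 5%, n = 6: 1 - 0.95^6 = 0.265. Table: 0.265.
- p = 5%, n = 12: 1 - 0.95^12 = 0.460. Table: 0.460.
- Rate detectable with 80% probability, 1 - 0.2^(1/n): 23.5% for n = 6 and 12.6% for n = 12. Text: 24% and 13%.

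These figures are right. They assume that every event that occurs is recorded.

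**Incomplete recording in general.** If a share s of events is recorded, the detectable rate is divided by s. With s = 0.5 it becomes 0.235/0.5 = 47% for 6 subjects and 0.1255/0.5 = 25% for 12.

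**Unequal recording by site.** P(groin-only pattern) = P(at least one of 6 in groin) × P(none recorded of 6 in deltoid) = [1 - (1 - p)^6] × (1 - sp)^6.

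| True rate p | s = 1 (equal) | s = 0.5 | s = 0 |
|---|---|---|---|
| 24% | 0.807 × 0.76^6 = 0.16 | 0.807 × 0.88^6 = 0.37 | 0.81 |
| 10% | 0.469 × 0.90^6 = 0.25 | 0.469 × 0.95^6 = 0.34 | 0.47 |

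At 24% with s = 0, the expected counts are 6 × 0.24 = 1.4 in the groin against 0 in the deltoid, although the true rates are equal.

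**Would a test flag it?** With 6 against 6 and none recorded in the deltoid, Fisher's exact test reaches 0.05 only from 5 against 0. At a true rate of 30% that has probability 6 × 0.3^5 × 0.7 + 0.3^6 = 0.011. The distortion would appear in the listing of events, rarely in a p-value.

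**The case against.** A reader might infer that node reactions will be missed altogether, or seen in the groin arm only. The documents do not support that.

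- Open routes of capture exist in both arms. The local item ends with a category for other effects that subjects report, adverse experiences are assessed at the post-dose visits, phone contact can lead to an in-person evaluation, and Section 10.1 promises monitoring of physical parameters and self-report. Section 4.1 says that efforts focus on the 5.1 list, not that they stop there. A painful axillary node in a deltoid subject would be reportable.
- The case report form, diary, adverse experiences form and severity grading guide are appendices that are not shown. Any of them may list nodes. The absence is shown only for the protocol body.
- Tenderness is a listed local reaction. In the groin it could already pick up a tender inguinal node.
- The area around the injection site is undefined. That it takes in one node region and not the other is a reading, though a natural one given the anatomy in Sections 2.0 and 9.
- The 81% needs full recording in one arm and none in the other, and the groin-only pattern occurs 16% of the time even with equal examination.
- No formal safety contrast between sites is specified. Section 1.2 compares the sites on immunogenicity, and the group tests in Section 6 follow the cellular assay results.

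All of this stands and limits the point. It does not remove it. Open reporting depends on symptoms, so it does not secure painless enlargement, and it does not make examiners look equally at both sites. With 6 vaccinees per site, the descriptive picture is the main safety result.

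**Conclusion.** The point holds as an inexpensive improvement. The body text names no node reaction in Section 5.1 and no node examination at any visit, although the primary objective is the safety of node-targeted vaccination. Followed as written, it may under-record node findings, especially painless ones, and record them unequally by site.

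The size cannot be fixed from the documents. Under the stated assumptions, unequal recording raises the chance of a groin-only pattern from 16% to between 37% and 81% at a 24% rate, and from 25% to as much as 47% at a 10% rate. The upper figures are extremes. It would be too strong to say that reactions go unseen, or that a formal comparison is biased: symptomatic nodes can be reported in either arm, and no such comparison is planned. If the unseen forms already carry a node item examined alike in both arms, what remains is to bring Section 5.1 and the visit lists into line with them.

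**What to change.** Add to Section 5.1: enlargement or tenderness of draining lymph nodes (inguinal, axillary, supraclavicular). In the visit lists, record the same node regions on both sides of the body, in every subject whatever the route. Do this at Day 0 before dosing and at each existing visit with an injection-site examination (Days 3 to 24 and month 6). Bring the calendar and the summary table into agreement on Day 14 and month 6, and align the wording with the case report form and grading guide.

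Three features of the design support identical regions and a Day 0 baseline. Injections alternate sides, so after Day 7 the opposite side is not an untreated control. The complete physical examination at Day -42 precedes the baseline biopsies. Section 2.0 says that inguinal nodes also drain the rectal tract, so by inference biopsies could produce inguinal findings in any arm; examining the groin in deltoid subjects helps to separate these from a vaccine effect.

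The cost is a few extra minutes of palpation per visit, including the groin in deltoid subjects, which is not part of their current site check, and some incidental node findings. No visit is added, and no dose or clinical rule changes.

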**Analysis:**

Interpretation to date from our previous vaccinia-based HIV vaccine trial is trending to support the belief that while peripheral immunization can induce peripheral immune responses, it does not necessarily induce mucosal responses. We have seen seroconversion peripherally with induced false-positive HIV ELISAs but effectively no indication of detected mucosal immune responses. This is in a setting of optimized assays and frequent samplings. Nevertheless, it is possible that sampling was scheduled at too great an interval following antigen exposure or the absorbed (humoral) or expanded (cellular) yields are too small to be reflective of mucosal responses. In the previous trial, we have demonstrated high trial adherence by subjects as well as optimization of mucosal assays (in press Journal Immunologic Methods). It is significant that using improved and optimized mucosal techniques; we are not finding mucosal responses in the presence of peripheral seroconversion.

The present protocol using vCP205, without boost, on a more condensed immunization schedule with more immediate mucosal assessments using the same immune response readouts will help elucidate whether these absences persist using a different vaccine with a different expression mechanism on a different schedule.

- 1. **Power calculations for identifying adverse experiences**

